## Results

The protocol was funded in May 2024 by the NIDA under the award number 1K01DA058768-01A1. The research team has developed a social media campaign (eg, Facebook and Instagram) to facilitate recruitment for formative qualitative interviews. As of February 10, 2025, the study has received 379 responses, with 24 (6.3%) completing screening interviews. In total, 8 participants who are identified as eligible for the study have consented and completed formative interviews (Figure 4).

Formative interviews (aim 1) are expected to be completed by May 2025. The completion of formative qualitative analyses and intervention module development (aim 2) is anticipated by May 2027. A protocol for an intervention study (aim 3) will be submitted to the Institute Review Board for Human Research for review in early 2027. Upon receipt of an approval, the recruitment of the RCT will be initiated in late 2027, and the intervention will be conducted in early 2028. The intervention feasibility and preliminary efficacy (aim 3) will be finalized by the middle of 2028. Data analyses and manuscript development of the intervention will be completed by the end of 2029.

**Figure 4 figure4:**
[figure not shown]
Recruitment progress for the formative study (aim 1) as of February 10. NMUPO: nonmedical use of prescription opioids.

## Discussion

### Anticipated Findings

In response to the growing evidence on psychosocial aspects of opioid addiction and relevant disorder concerns in the United States, this proposed study aims to apply a psychosocial theoretical framework and peer role model techniques to develop and implement an evidence-based intervention for reducing NMUPO risk in young US adults. The intervention will be established through a serial research activity, from a formative semistructured in-depth interview study to feasibility evaluation of a 12-week interactive peer-led trial. By leveraging the merits of social media, the proposed intervention study will be powered by adopting innovative approaches, including a tailored recruitment strategy (eg, paid advertisement campaigns), intervention delivery that transcends time and space constraints, and the application of mixed methods and time-series assessments (eg, paradata and EMA measures). As one of the first attempts to deliver peer-led interventions on social media specifically targeting NMUPO, the findings from this mixed methods design will offer valuable insights into the use of innovative approaches for reducing opioid risk among young adults. In line with previous intervention studies for NMUPO on social media [45], we anticipate that our intervention will yield high feasibility outcomes. In particular, the mixed methods assessments for the intervention group will demonstrate (1) high feasibility, acceptability, and usability on all intervention modules among young adults across 12 weeks and (2) high engagement, especially for the modules in the interactive formats, such as discussion polls and live streaming group meetings. We also anticipate significant preliminary intervention efficacy on the NMUPO-related and psychosocial behavior outcomes. Compared to the control group, the intervention will report (1) decreases in past–3-month NMUPO and other substance use (eg, alcohol, illicit drugs, and cigarettes), (2) decreases in psychological distress, (3) changes in outcome expectancies (eg, increased physical discomfort and decreased pain reduction), (4) increases in NMUPO knowledge and NMUPO risk perception, and (5) increases in resilience and self-efficacy (ie, action and coping).

Notably, the proposed intervention will be developed and implemented based on qualitative findings on the psychosocial mechanism of NMUPO, incorporating tailored psychotherapy strategies, such as CBT, MI, and peer role models. As highlighted in recent research, NMUPO in young adults is robustly driven by psychosocial factors, with influences comparable to biological and medical factors, which are traditionally viewed as prominent determinants [22]. However, scant theory- and evidence-based intervention programs have been designed to empower psychosocial skills for young US adults, especially for those who have engaged in NMUPO but do not develop addiction or SUDs. As a pilot trial, our feasibility evaluation will contribute to emerging practices of opioid use disorder prevention within social media settings, particularly through the implementation of peer-led groups [45,46]. In addition, preliminary efficacy on psychosocial measures will contribute to the growing literature on psychosocial aspects of NMUPO and offer clinical evidence for using psychosocial intervention to manage the risk of opioid misuse in the young population. The success of the proposed trial should underscore the potential of leveraging social media as a feasible tool for delivering secondary prevention programs targeted at group-based psychosocial skill training for young people at high risk of SUD.

The proposed study has several methodological limitations. First, the generalization of our findings will be limited by the convenient sampling approach. Second, because most evaluations in this study will be based on self-reported measures, results could be subject to response bias (eg, social desirability and recall bias). Third, our EMAs could impose additional burdens on participants due to the frequent prompts for assessments in real time. Fourth, our efficacy findings could be limited in assessing long-term effects given a pre- and postevaluation design. Fifth, since the planned content for all peer-led groups will be identical and delivered concurrently, our analyses could not examine the efficacy of specific intervention modules. Sixth, given a program will be delivered on Instagram, our findings will be limited to Instagram users, and the format and presentation of the intervention content will be constrained by the platform’s available features and functionality. Seventh, our peer leaders could also have limitations. They are recruited solely from local agencies within a single state (South Carolina). In addition, although they will be supported by clinicians (eg, licensed clinical psychologists and physicians in addiction medicine), their service may be subject to disparities in the quality of support. To address those, our future plan is to conduct a scaled-up cross-platform social media RCT study with a design of the multiphase optimization strategy and longitudinal measures. The intervention will be provided by a team of peer leaders, comprising recovery coaches with expertise in opioid misuse from various states across the United States.

The proposed intervention might encounter several potential challenges related to social media, including inefficient recruitment (eg, scams) and intervention delivery affected by the policy changes to social media platforms. Several contingency plans will be used if these occur. To address recruitment challenges, the eligibility of participants will be thoroughly evaluated by a 2-step approach. Young adults who have signed up for participation via social media will be navigated to complete a screening survey regarding their age, current NMUPO, history of SUDs, and their preferred online meeting methods. The research team will then contact the participants by their preferred methods and evaluate their eligibility in person. In addition, the recruitment plan will be supplemented by additional in-person approaches, including a snowball strategy (ie, allowing participants to invite eligible peers), and an outreach approach (ie, advertising at local young adult communities, colleges, and associations). To address the policy challenges to social media, the research team will transfer multimedia files to a publicly available but password-secured platform (eg, Discord [Discord Inc]), which also allows member reactions, and implement all interactive activities (eg, live streaming) via alternative social media applications (eg, WhatsApp [Meta Platforms]).

Guided by a theoretical framework, the proposed intervention study is dedicated to reducing NMUPO behaviors and the risk for opioid-related addiction and disorders by empowering psychosocial competencies among young adults via the application of social media. The proposed program is informed by substantial literature on NMUPO in young adults and formative qualitative findings of psychosocial mechanisms associated with NMUPO behavior management. Findings from rigorous methods are anticipated to inform a future scaled-up RCT study to optimize intervention content and effectiveness of a fully powered cross-platform social media intervention.

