#### Aim 3: Intervention Feasibility and Preliminary Efficacy Evaluation Study

##### RCT Design

The intervention modules will be tested through an RCT design using mixed methods in 70 young adults who engage in NMUPO [93]. The primary purpose is to determine acceptability, usability, feasibility, and initial efficacy. Participants reached by peer leaders or advertisements on social media will be navigated to a screening survey on REDCap and scheduling a meeting with the research team for informed consent. Participants will be required to comply with the user safety agreement. Participants will be randomly assigned to the parallel intervention (35/70, 50%) or control group (35/70, 50%) using computer-generated random numbers. Participants are blinded to the randomized assignments. Intervention group will be guided to join Instagram peer-led private groups (n=10-15 each). Participants will be asked to provide their Instagram accounts to their assigned peer leaders for participating in intervention activities. Peer leaders will set up private and independent groups via their Instagram accounts and will send direct invitations to their assigned participants to join groups. Once group membership is confirmed, peer leaders will post intervention materials and lead group activities according to the plan as developed in aim 2. Private groups will synchronously deliver intervention packages over 12 weeks. To ensure confidentiality, participants will be assigned unique study IDs, which will be used for data collection and intervention activities. The intervention group will participate in data collection through multiple formats, including Instagram paradata, pre- and postintervention surveys, EMA surveys, and postintervention semistructured interviews.

The control group will not engage in any intervention activities but will complete the pre- and postintervention surveys.

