##### Outcome Expectancies

Beliefs on positive or negative consequences of engaging in NMUPO will be assessed using a scale adapted from the Behaviors, Expectancies, Attitudes, and College Health Questionnaire [101]. A total of 50 items will be scored on a 5-point Likert-type scale ranging from 0 (not at all) to 4 (very often or always), with higher sum scores standing for the greater level of expectancies. The scale consists of 8 dimensions related to specific expectancies of opioids, including pain reduction, tension reduction, academic preference, emotion enhancement, social enhancement, guilt and dependence, cognitive impairment, and physical discomfort.

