##### Psychological Distress

Depression and anxiety symptoms in the past 2 weeks will be assessed using the Patient Health Questionnaire-9 [104] and Generalized Anxiety Disorder-7 [105], respectively. The Patient Health Questionnaire-9 is composed of 9 items asking the frequency of depressive mood experiences (eg, “feeling down, depressed, and hopeless”), while the Generalized Anxiety Disorder-7 comprises 7 items assessing the frequency of feelings of nervousness or worry (eg, “not being able to stop or control worrying”). Two scales have 4 response options ranging from 0 (not at all) to 4 (nearly every day). Sum scores for 2 scales will be generated, with higher scores indicating greater levels of depression or anxiety.

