##### Multivariate Analyses

Preliminary outcomes from baseline and 12 week will be tested using repeated measures analysis of covariance, controlling for demographics. EMA data will be tested using multilevel modeling (ie random-coefficient regression model) to examine intervention usability and acceptability, capable of incorporating tests of time-serial characteristics, including linear trend over time and cyclicity. Before multilevel modeling, unconditional means models will be tested for between- and within-participant variation in each measure and determination of appropriate within-person error covariance structure [108].

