### Power Analysis

The primary aim is to evaluate the feasibility, acceptability, and usability of the intervention to support a future large-scale RCT. According to the guidance for pilot intervention studies [110], it is suggested a minimum sample of 30 per group for the feasibility evaluation. In terms of the aim for the preliminary efficacy evaluation (ie, secondary outcomes of psychosocial and behavioral factors associated with NMUPO), we estimate an effect size according to a previous review on digital interventions for illicit drug use [111] and found small-to-medium effect sizes (Cohen *d*=–0.17 to –0.34) with a 6-month follow-up assessment. G-power analysis [112] estimated a sample size of 10 to 35 per arm for an RCT (repeated measures analysis of covariance). According to previous mHealth trials for substance use with retention rates ranging from 75% to 93% [46,53,61], a sample of 70 appears to be feasible and provides adequate power for proposed analytic plans. Despite a small sample size, this is appropriate for the aim of developmental research.

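### Efficacy is part of the primary purpose in one section and secondary in the others, and significance is anticipated across at least ten unranked outcomes, so an isolated significant result would be weak evidence

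*Protocol article*

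**What the plan says.** The protocol article gives efficacy two different ranks. Under RCT Design it states: "The primary purpose is to determine acceptability, usability, feasibility, and initial efficacy". Under Power Analysis it states: "The primary aim is to evaluate the feasibility, acceptability, and usability of the intervention to support a future large-scale RCT", and efficacy follows there as a separate aim on secondary outcomes. The Abstract, the Measures heading for the web-based surveys and Bivariate Analyses also class the psychosocial and behavioral measures as secondary.

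The efficacy analysis is a single sentence under Multivariate Analyses: "Preliminary outcomes from baseline and 12 week will be tested using repeated measures analysis of covariance", with adjustment for demographics. It covers the outcomes together and gives no order among them.

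The Discussion, under Anticipated Findings, then says: "We also anticipate significant preliminary intervention efficacy on the NMUPO-related and psychosocial behavior outcomes". Five groups of expected differences from control follow, beginning with "decreases in past–3-month NMUPO and other substance use". The next paragraph says that preliminary efficacy on the psychosocial measures will provide clinical evidence for this type of intervention.

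The recall window for NMUPO also varies. It is the past month under Aim 3, and the past 3 months in the Abstract, in the section on the pre- and postintervention surveys and under NMUPO Measurement.

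**The concern.** Efficacy cannot be both part of the primary purpose and secondary. The difference matters when the results are read: a result that bears on a primary purpose carries more weight than one among many secondary measures.

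The article also raises an expectation of statistical significance over a long list without saying which outcome carries the efficacy question. When many outcomes are tested and none leads, one significant result is easy to obtain by chance. The limitations paragraph lists seven points, and the number of outcomes tested is not among them. At stake is what the pilot may conclude about efficacy.

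**Working it through.** **1. Rank of efficacy, place by place**

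| Place | Rank |
|---|---|
| Abstract, Methods | secondary |
| RCT Design | part of the primary purpose |
| Measures, heading for the web-based surveys | secondary |
| Bivariate Analyses | secondary (feasibility is primary) |
| Power Analysis | secondary (the primary aim is feasibility, acceptability and usability) |

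RCT Design stands alone against the other four.

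**2. Number of outcomes**, from the list in Anticipated Findings and the scoring rules in Measures

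- NMUPO and other substance use: 2.
- Psychological distress: 2, because depression and anxiety are scored separately ("Sum scores for 2 scales will be generated, with higher scores indicating greater levels of depression or anxiety").
- Outcome expectancies: 1 as a total score. However, "The scale consists of 8 dimensions related to specific expectancies of opioids", and Anticipated Findings predicts a rise in one dimension and a fall in another, which a single total would not show.
- "increases in NMUPO knowledge and NMUPO risk perception": 2.
- Resilience: 1.
- Action and coping self-efficacy: 2, because each subscale has its own sum score.

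Total: 2 + 2 + 1 + 2 + 1 + 2 = 10. With the 8 expectancy dimensions counted singly: 10 − 1 + 8 = 17.

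**3. Chance of at least one significant outcome when no effect is real**

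The article states no significance level, so two-sided 0.05 per test is assumed. It gives no correlations between outcomes either, so a range is shown.

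For k independent tests, the chance of a significant result in either direction is 1 − 0.95^k:
- k = 10: 1 − 0.599 = 0.401
- k = 17: 1 − 0.418 = 0.582

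Counting only favourable results, each test has a chance of 0.025, and the formula becomes 1 − 0.975^k:
- k = 10: 1 − 0.776 = 0.224
- k = 17: 1 − 0.650 = 0.350

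For correlated outcomes, k normal test statistics with a common correlation, aligned in the direction of benefit, were simulated:

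| Outcomes | Correlation | Either direction | Favourable only |
|---|---|---|---|
| 10 | 0 | 40% | 22% |
| 10 | 0.3 | 35% | 18% |
| 10 | 0.5 | 29% | 14% |
| 10 | 0.7 | 21% | 11% |
| 17 | 0 | 58% | 35% |
| 17 | 0.3 | 49% | 25% |
| 17 | 0.5 | 39% | 19% |
| 17 | 0.7 | 27% | 13% |

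With one named lead outcome the corresponding chances are 5% and 2.5%.

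**4. Recall window of the natural lead outcome.** Aim 3 has one month. The Abstract, the survey section and NMUPO Measurement have three months. Naming NMUPO as the lead outcome without settling this would leave the lead outcome defined in two ways.

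**The case against.** - **This is a pilot, and its efficacy is called preliminary throughout.** True, and it favours estimates with confidence intervals over an expectation of significance.
- **Ranking of secondary outcomes and handling of multiplicity may sit in an analysis plan that is not shown.** This stands. The absence of a named key outcome is not a finding by itself, and no multiplicity adjustment is asked for here. The point rests on what the article states: two ranks for efficacy, and significance anticipated over an unranked list.
- **Anticipated Findings is a forecast and not a decision rule.** This stands too. A reader might infer that any one significant outcome would be declared preliminary efficacy. No section says so; the Discussion predicts a pattern across all outcomes, mostly with stated directions.
- **40% and 58% overstate the risk.** They are the figures for independent tests in either direction. Depression, anxiety, resilience and self-efficacy are plausibly correlated, and a significant harmful result could not be presented as efficacy. The lower figures in the table are the fairer guide. For expectancies, though, only two dimensions are given a direction, as examples, so what counts as favourable is not fully defined there.
- **A chance result would not steer the full trial.** A reader might infer that it would choose the target of the later RCT. The documents do not support this: the Abstract makes scale-up depend on feasibility, and the target is already reduction of NMUPO.
- **The contradiction is one loose sentence.** It is, and that keeps the point small. It still needs correcting, because it stands in the section that defines the trial's purpose.

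**Conclusion.** The point holds in limited form. RCT Design contradicts the Abstract, Measures, Bivariate Analyses and Power Analysis on the rank of efficacy. Separately, the article anticipates significance over at least 10 unranked outcomes tested with one model. Under an assumed two-sided 0.05 per test and no true effect, at least one of 10 would be significant with a chance of 40% if independent and about 21% to 35% at correlations of 0.7 to 0.3. For favourable results only, the chance is at most about 22%, assuming independent or positively correlated outcomes. An isolated significant result would therefore be weak evidence of efficacy.

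The contradiction and the unranked list do not depend on these assumptions; only the percentages do. The power of 35 per arm at the effect sizes cited under Power Analysis is a separate matter, and this conclusion does not need it.

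**What to change.** 1. In RCT Design, delete initial efficacy from the primary purpose, so that it agrees with the other sections.
2. Name NMUPO as the single lead efficacy outcome, and reconcile its recall window between Aim 3 (past month) and the Abstract, survey section and NMUPO Measurement (past 3 months).
3. Report the other outcomes as exploratory between-arm differences with 95% confidence intervals and no significance claims.
4. In Anticipated Findings, replace the expectation of significance with the expected direction and size of each difference, to be reported with its interval.

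No adjustment of the significance level is needed. The cost is wording only, and there is time: the results section plans submission of the intervention protocol for ethics review in early 2027. The downside is that the sponsor gives up efficacy claims based on isolated significant secondary outcomes.

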### Study Dissemination

To promote the academic and social benefits of the proposed intervention study, several strategies will be used to disseminate the study findings. First, the findings will be published in international and national scientific journals and presented at national and international scientific meetings or conferences held by SUD research institutes. Second, the access to the deidentified data will be available for registered users through our selected data repository, the Interuniversity Consortium for Political and Social Research, with high security standards. Third, documentation and support materials regarding the intervention will be available at ClinicalTrials.gov and compatible with its protocol registration data elements. Fourth, we will capitalize on social media and professional networks that can increase the research and accessibility of findings, such as webinars, files, and videos available on websites and publicly available channels (eg, YouTube [Google LLC]), to increase the visibility and impact of the scientific publications and presentations. We hope that the anticipated success of the proposed intervention will prompt policy attempts for prescription drug intervention and treatments. The lessons learned from the proposed study and the intervention strategies tested can be scaled up to reduce NMUPO risk in young adults and other high-risk populations.

## Appendix

Multimedia Appendix 1 SPIRIT (Standard Protocol Items: Recommendations for Intervention Trials) checklist for the proposed study.

Multimedia Appendix 2 Peer-review report from the IPTA–Interventions to Prevent and Treat Addictions Study Section, National Institute on Drug Abuse (National Institutes of Health, USA).

Multimedia Appendix 3 CONSORT-eHEALTH checklist (V 1.6.1).

